### Preoperative Workup

Approximately one month prior to surgery, patients will undergo preoperative evaluations, including an abdominopelvic computed tomography (CT) scan, a loopogram with rectal iodinated contrast, a digital rectal examination, and rectoscopy. During rectoscopy, any changes in the mucosa or anastomosis site will be meticulously documented. If such changes are observed, biopsies will be taken as part of standard care for patients with rectal cancer during oncological follow-up. A comprehensive preoperative clinical and anesthetic evaluation will also be conducted.

### Probiotics Administration

The patients will receive a 14-French Foley catheter, normal saline, and probiotics (Lacidofil®) containing *Lactobacillus rhamnosus* R0011 and *Lactobacillus acidophilus* R0052 bacterial culture (2×109 colony-forming units) in an outpatient setting. This formulation was considered appropriate for the present trial because Lactobacillus-based probiotics have been investigated in colorectal and other gastrointestinal settings as microbiota-modulating interventions, although evidence remains inconclusive regarding their effect on postoperative bowel function and LARS [20]. The probiotic dose was selected to ensure a practical and standardized daily regimen for outpatient administration while remaining aligned with the commercially available formulation and with doses that have been evaluated in prior studies using the same product or closely related probiotic preparations [21]. The intervention group will receive 250 mL of normal saline with 4 g of Lacidofil® administered via the distal limb of the ileostomy once daily for 2 weeks prior to ileostomy closure. The control group will receive 250 mL of normal saline without probiotics using the same method. The 250 mL of normal saline will be infused over 10‐15 minutes via a 14-French Foley catheter with the patient in a supine position. Adherence will be monitored through daily patient diaries and weekly outpatient visits. Patients will record abdominal symptoms, including pain, nausea, vomiting, diarrhea, and gas and stool passage during the 2-week period before ileostomy closure.

### Surgical Techniques and Surgeons

Three experienced surgeons, each having performed over 50 ileostomy closure procedures, will conduct the surgeries. All patients will consume two 200 mL cans of a complex carbohydrate drink 2 hours before surgery and fast thereafter, receiving a second-generation cephalosporin as prophylactic antibiotic therapy. Ileostomy closure will be performed as follows:

Position the patient in a supine position under general anesthesia.Apply aseptic surgical drapes using alcoholic chlorhexidine and povidone-iodine solutions.Make a circular incision around the ileostomy, dissecting in layers until the ileostomy is released from the aponeurosis.Perform ileostomy closure with a side-to-side anastomosis using linear staplers.Ensure hemostasis and close the wound layer by layer.

### Postoperative Management and Follow-Up

Oral intake will begin the day after ileostomy closure unless obstructive symptoms are reported. Hospital discharge will be determined by the surgeon based on adequate pain control without the need for intravenous or intramuscular analgesics, tolerance of a soft diet, independent ambulation, and absence of significant complications or other medical concerns. Patients will be followed for at least 3 months post-surgery, with visits at 1 week and 1 month. At each visit, patients will be assessed and questioned regarding food acceptance via patient-reported dietary intake logs, stool habits using the Bristol Stool Chart and daily frequency records, and laboratory tests. Three months post-surgery, patients will complete the LARS questionnaire in an outpatient setting. The detailed schedule of assessments is presented in Figure 1.

**Figure 1. F1:**
[figure not shown]
Standard Protocol Items: Recommendations for Interventional Trials (SPIRIT)-compliant schedule of enrolment, interventions, and assessments. CT: computed tomography; DRE: digital rectal exam; LARS: low anterior resection syndrome.

### Outcomes

The primary outcome is the LARS score at 3 months after ileostomy closure. The LARS score is a validated patient-reported outcome measure based on 5 items: incontinence for flatus, incontinence for liquid stools, bowel frequency, clustering of stools, and urgency. The total score ranges from 0 to 42, with higher scores indicating more severe bowel dysfunction. Scores are categorized as no LARS (0‐20), minor LARS (21-29), and major LARS (30-42). The questionnaire will be administered in the outpatient clinic at 3 months postoperatively.

The secondary outcomes include (1) postoperative complications within 30 days after ileostomy closure, including ileus, surgical site infection, anastomotic-related complications, readmission, and reoperation; (2) severity of postoperative complications, graded according to the Clavien-Dindo classification; (3) bowel recovery parameters, including time to first flatus, time to first stool passage, and tolerance of oral intake; (4) stool habits, including stool frequency and stool form assessed using patient records and the Bristol Stool Chart; (5) laboratory findings obtained during follow-up; and (6) length of postoperative hospital stay.

Patients will enter an open follow-up phase for up to 5 years for routine postoperative surveillance, monitoring oncologic outcomes and late complications through periodic clinical visits and imaging studies per institutional guidelines.

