### Sample Size Calculation

The sample size calculation was based on the primary outcome, the LARS score at 3 months after ileostomy closure. Based on a previous study [21], we considered a 3-point between-group difference in LARS score to be clinically relevant. For the sample size estimation, the standard deviation was conservatively assumed to be 5 points. Using a 2-sided significance level of .05 and 80% power, 45 participants were required per group. Allowing a 10% dropout rate, the final target sample size was set at 100 participants (50 per group).

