### Statistical Analysis

Results will be presented as means with standard deviations for continuous variables and as frequencies and percentages for categorical variables. The *χ*^2^ test or Fisher exact test will be used for categorical data, while the Student’s t-test or Mann-Whitney *U* test will be applied to continuous data. Logistic regression will be conducted for univariate and multivariate analyses. For adjusted analyses, prespecified covariates will include age, sex, body mass index, tumor location, clinical stage, neoadjuvant treatment history, operative approach, anastomotic level, and the interval between index rectal surgery and ileostomy closure. Exploratory subgroup analyses may be performed according to sex, age group, operative approach, and anastomotic level. Because the study is not powered for subgroup comparisons, these analyses will be interpreted cautiously. A *P* value <.05 will be considered statistically significant.

Analyses will be conducted on an intention-to-treat basis, including all randomized participants in their assigned groups, regardless of protocol adherence. A per-protocol analysis will be performed as a sensitivity analysis to assess result robustness. For missing data, multiple imputation methods will be employed, assuming data are missing at random. Sensitivity analyses will evaluate the impact of missing data on primary and secondary outcomes. Statistical analyses will be conducted using SPSS software (version 25; IBM Corp., Armonk, NY, USA).

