### Data Collection and Monitoring

Data will be collected using a standardized case report form and entered into a Microsoft Access database. Collected data will include demographic characteristics, baseline clinical variables, perioperative findings, intervention adherence, patient-reported bowel symptoms, dietary intake logs, Bristol Stool Chart records, laboratory results, postoperative complications, and follow-up outcomes including the LARS questionnaire. Data accuracy will be monitored through double data entry and weekly audits.

Participant retention will be promoted through reminder calls and flexible outpatient visit scheduling. Regardless of findings, results will be submitted for publication in a peer-reviewed journal. A data monitoring committee is not required, as probiotics are classified as low-risk interventions per International Council for Harmonisation (ICH) Good Clinical Practice (GCP) guidelines and prior studies [12,15]. No interim analyses are planned, and the study will conclude upon data collection completion unless unexpected adverse events prompt a halt and review.

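### The text gives only a clinic visit for completing the single 3-month LARS score, so a participant who does not attend has no observed primary outcome

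*Protocol article*

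**What the plan says.** The Outcomes section of the protocol article defines the endpoint: "The primary outcome is the LARS score at 3 months after ileostomy closure". It describes a five-item patient-reported instrument scored 0 to 42 and fixes where it is completed: "The questionnaire will be administered in the outpatient clinic at 3 months postoperatively". Postoperative Management and Follow-Up repeats this: "Three months post-surgery, patients will complete the LARS questionnaire in an outpatient setting".

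The earlier contacts are set out in the same section: "Patients will be followed for at least 3 months post-surgery, with visits at 1 week and 1 month". They record dietary intake and "stool habits using the Bristol Stool Chart and daily frequency records, and laboratory tests". No LARS questionnaire is mentioned at those visits.

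On retention, Data Collection and Monitoring says: "Participant retention will be promoted through reminder calls and flexible outpatient visit scheduling". The Statistical Analysis section keeps all randomized participants in their assigned groups whatever their adherence, and adds: "For missing data, multiple imputation methods will be employed, assuming data are missing at random". It also plans sensitivity analyses for the impact of missing data, without naming their type. The Sample Size Calculation allows for 10% dropout.

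**The concern.** The primary analysis rests on one score per participant, and the text offers one way to obtain it. Reminder calls and flexible scheduling make attendance more likely, but they give no route to a score when the visit does not happen. The instrument asks about flatus incontinence, liquid stool incontinence, frequency, clustering and urgency. These are symptoms that could plausibly keep someone from travelling to a hospital, so whether the score is missing may depend on what the score would have been.

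If so, missing at random is doubtful. Imputation has baseline variables and early stool records to work with. Of the five items, however, only bowel frequency has a clear counterpart in those records, and there is no earlier LARS score. Sensitivity analyses can show how fragile the result is, but they cannot recover a score that was never collected. What is at stake is precision in every case, and bias in the between-group difference if loss, or the reasons for it, differ between arms.

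**Working it through.** **1. The plan's own sample size.** Inputs from Sample Size Calculation: difference 3 points ("we considered a 3-point between-group difference in LARS score to be clinically relevant"), SD 5, two-sided alpha .05, power 80%, dropout 10%.

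- Normal approximation: n = 2 × (1.960 + 0.842)² × 5² / 3² = 43.6, so 44 per group.
- t-test solution: 44.59, so 45 per group, as stated.
- Dropout: 45 / 0.90 = 50 per group, 100 in total, as stated.

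The stated figures reproduce.

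**2. Precision.** Two-sample t-test power at difference 3 and SD 5, by number scored per arm:

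| Scored per arm | Missing | Power |
|---|---|---|
| 50 | 0% | 84.4% |
| 45 | 10% | 80.4% |
| 40 | 20% | 75.5% |
| 35 | 30% | 69.7% |

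The 10% allowance protects the nominal 80%, with almost no slack beyond it. The 84.4% is a ceiling that needs every score, which no fallback can guarantee.

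**3. Bias in a complete-case comparison.** Let f be the fraction missing in an arm, and d the number of points by which non-attenders score worse than attenders in the same arm. The true arm mean is (1 − f) × A + f × (A + d) = A + f × d, where A is the attenders' mean. The observed mean is therefore too low by f × d. With a true benefit of 3 points (control minus probiotic):

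observed benefit = 3 − (f control − f probiotic) × d

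The documents give no loss rates by arm and no value for d, so the figures below are assumptions.

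| Missing, probiotic | Missing, control | d = 5 | d = 10 |
|---|---|---|---|
| 10% | 10% | 3.0 | 3.0 |
| 5% | 15% | 2.5 | 2.0 |
| 15% | 5% | 3.5 | 4.0 |

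The shift is 0.10 × 5 to 0.10 × 10 = 0.5 to 1.0 point, or 0.5/3 = 17% to 1.0/3 = 33% of the target difference. With d = 3 it is 0.3 point (10%). Overall loss is 10% in all three rows, so the plan's dropout allowance says nothing about this bias. Imputation that uses the stool records may remove part of it; the table assumes it removes none.

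**The case against.** The strongest reply is that this is an article, not the full protocol. The sections name a usual setting and exclude no other; how non-attenders are followed up is operational detail; Figure 1, the assessment schedule, is not shown. This stands in part: that the clinic is the only route is established for the available text alone. But the place of completion is stated twice, and the retention measures are framed around outpatient visits, so this is a described choice and not just silence.

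Several further points stand:

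- A reader might infer that patients who stop the instillations lose their outcome. The documents do not support that. The instillations end before closure, the score is due 3 months after it, and the Statistical Analysis section retains everyone regardless of adherence. The text only fails to separate stopping treatment from leaving follow-up.
- A reader might also infer that non-attendance is probably driven by bowel function. The documents give no rates or reasons. Patients with worse symptoms may equally be keener to be seen, and all participants have routine cancer surveillance as a reason to attend.
- The lack of an earlier LARS score is partly inherent, since the items have little meaning while stool is diverted.
- The bias illustration needs loss three times as high in one arm as in the other and a gap of 1 to 2 SDs (5 to 10 points against SD 5). Both arms follow the same instillation procedure, and no mechanism for unequal loss is evident.
- One uniform mode for a subjective outcome is defensible, and a fallback would mix modes among the patients most likely to differ.

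These points limit how strongly the concern can be put. They do not remove it: a missed visit still means a missing primary outcome that could have been collected without a visit.

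**Conclusion.** The point holds in a limited form. As the text stands, the single primary score depends on attendance at a clinic visit, and no other way to complete it is described. Missing at random may fail for those who do not attend, and the planned imputation, helped by early stool records, may not fully correct for this.

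The size is conditional. Under an assumed 10-point imbalance in loss and a 5 to 10 point gap, a complete-case difference moves by 0.5 to 1.0 point, towards or away from the null depending on which arm loses more. Under equal loss for the same reason there is no bias, only lower power. Nothing in the documents shows which case applies. No stated figure is wrong, and the sample size reproduces. This is a worthwhile, inexpensive improvement to outcome collection.

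**What to change.** Keep the clinic visit as the default. In Outcomes and in Postoperative Management and Follow-Up, state that any randomized participant with restored bowel continuity who misses the visit and has not withdrawn consent to contact, whatever their adherence to the instillations, completes the same questionnaire by telephone, post or online within the same 3-month window. Record the mode of completion. The reminder calls already planned can carry this.

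The cost is protocol wording and one case report form field; treatment, eligibility and sample size do not change. The downside is a minority of scores from a different mode, which a sensitivity analysis by mode can check. Enrolment had not begun when the manuscript was submitted, so if the change is made before the first participant enters it covers everyone. If the full protocol already provides a remote option, saying so in these two sections is enough.

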### Sample Size Calculation

The sample size calculation was based on the primary outcome, the LARS score at 3 months after ileostomy closure. Based on a previous study [21], we considered a 3-point between-group difference in LARS score to be clinically relevant. For the sample size estimation, the standard deviation was conservatively assumed to be 5 points. Using a 2-sided significance level of .05 and 80% power, 45 participants were required per group. Allowing a 10% dropout rate, the final target sample size was set at 100 participants (50 per group).

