### Randomization and Allocation

Participants will be randomly assigned to either study group in a 1:1 ratio using a computer-generated allocation sequence. To ensure allocation concealment, the sequence will be secured in sequentially numbered, opaque envelopes, open only after participant enrollment. These envelopes will be prepared by a study staff member independent of patient enrollment and data collection. To reduce bias, surgeons performing the operations will remain blinded to group assignment until after anesthesia is initiated.

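### The 80% power holds only at an SD of 5, which the plan calls conservative without a source, although 5 lies at the low, optimistic end for its own 0–42 scale

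*Protocol article*

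**What the plan says.** In the Outcomes section, "The primary outcome is the LARS score at 3 months after ileostomy closure", and "The total score ranges from 0 to 42, with higher scores indicating more severe bowel dysfunction". The same section divides the score into no LARS (0–20), minor (21–29) and major (30–42).

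The Sample Size Calculation section takes its difference from a cited study: "Based on a previous study [21]", after which "we considered a 3-point between-group difference in LARS score to be clinically relevant". The next sentence sets the spread without a citation: "the standard deviation was conservatively assumed to be 5 points". Then "Using a 2-sided significance level of .05 and 80% power, 45 participants were required per group", and "Allowing a 10% dropout rate, the final target sample size was set at 100 participants (50 per group)".

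The article gives no expected mean, SD or band distribution at 3 months, and does not show how power changes with the SD. For adjusted analyses, the Statistical Analysis section names logistic regression only.

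**The concern.** Required sample size grows with the square of the SD, so a cautious planner errs towards a large SD. Calling 5 conservative therefore tells the reader that the true SD is probably no larger and that 80% power is, if anything, an understatement. The article offers no source, observed value or range to support this, and the score's own range and cut points suggest that larger values are easy to reach.

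What is at stake is how a null result is read. Under a claim of 80% power, a non-significant difference will be taken as evidence against a 3-point benefit. If the SD is well above 5, the trial could easily miss such a benefit, and its confidence interval would not exclude it. The power claim is also fragile: one extra point of SD costs about 15 percentage points of power.

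**Working it through.** **Inputs from the article.** Difference 3; SD 5; two-sided alpha 0.05; power 80%; 1:1 allocation; 10% dropout; score 0–42; cut points 20/21 and 29/30.

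**1. The plan's own figure.** Normal approximation: n = 2(1.960 + 0.842)² × 5²/3² = 43.6 per group. The two-sample t calculation (noncentral t, standardised difference 3/5 = 0.6) gives 44.6, rounded up to 45. Dropout: 45/0.9 = 50 per group, 100 in total. Power at 45 per group is 80.4%. The stated figures reproduce.

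**2. What SD 5 implies on this scale.** With normal scores and SD 5, the cut points 20.5 and 29.5 lie 9/5 = 1.8 SDs apart.
- Mean 25: no/minor/major shares of 18/63/18%.
- Mean 30: 3/43/54%.

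An SD of 5 is therefore possible, but it requires most patients to sit in or next to the minor band, with about 95% inside a 20-point span.

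**3. SDs implied by other splits (assumed, because the article gives none).** For normal scores, SD = 9 / [z(1 − p_major) − z(p_no)]. For example, 10/40/50 gives 9/(0 + 1.282) = 7.0. Because the score is bounded, the last column refits a normal truncated to the scale (−0.5 to 42.5, allowing for whole-number scores).

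| No/minor/major, % | SD, untruncated | SD, truncated |
|---|---|---|
| 10/60/30 | 5.0 | 5.0 |
| 20/60/20 | 5.3 | 5.3 |
| 10/40/50 | 7.0 | 6.6 |
| 20/40/40 | 8.2 | 7.7 |
| 10/30/60 | 8.8 | 7.4 |
| 30/30/40 | 11.6 | 10.0 |

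The shape within bands also matters. With scores uniform within each band, 10/30/60 gives 9.1 and 50/25/25 gives 12.0. With tighter packing (no LARS limited to 10–20, major to 30–38), 10/30/60 gives 6.8 and 10/80/10 gives 5.0. With nobody in the no-LARS band, 0/50/50 gives 6.4 (uniform) or 5.2 (tight), and 0/30/70 gives 6.1 or 4.9.

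**4. Consequences at 45 evaluable per group.** Power is from the two-sample t-test. The detectable difference scales with the SD. The 95% confidence interval half-width is t(0.975; 88) × SD × √(2/45) = 1.987 × SD × 0.2108.

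| SD | Power for 3 points | Difference detectable with 80% power | 95% CI half-width |
|---|---|---|---|
| 5 | 80% | 3.0 | 2.1 |
| 6 | 65% | 3.6 | 2.5 |
| 7 | 52% | 4.2 | 2.9 |
| 8 | 42% | 4.8 | 3.4 |
| 10 | 29% | 6.0 | 4.2 |
| 12 | 22% | 7.2 | 5.0 |

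Retaining all 50 per group changes little: 56% at SD 7 and 32% at SD 10.

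**The case against.** A reader might infer that any ordinary spread over the three bands forces an SD of 7–12, so that true power is only about 20–50%. The documents do not support that. They give no band shares, and unremarkable splits such as 10/60/30 and 20/60/20 give 5.0 and 5.3. The untruncated normal model also overstates the upper values: at 10/30/60 it puts about 11% of patients beyond the top of the scale, and bounding the scores lowers 8.8 to 7.4 and 11.6 to 10.0. SDs near 12 arise only with other within-band shapes.

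Nor can one assume that patients will cover all three bands evenly. The eligibility criteria do not restrict anastomotic level, which argues for a mixed population. But every participant has had chemoradiotherapy and a diverting ileostomy, both listed in the Introduction as risk factors. Few patients may therefore be free of LARS, and in that case the implied SD falls to about 5–6.5.

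The cited study may report an SD, and it cannot be checked here. The article ties it to the difference, not to the SD. Finally, a null result is properly read from its observed confidence interval, not from planning power. That is true, and it is the reason to fix the interpretation rule in advance.

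These points remove any claim that the true power is known to be low. They do not supply a basis for calling 5 conservative.

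**Conclusion.** The concern holds in a limited form. There is no arithmetic error: 45 per group and 80% power follow from the stated inputs. The fault is an unsourced SD presented as cautious when, on the plan's own scale and bands, it is at the favourable end: about 5.0–5.3 for clustered splits, about 6.6–10 for broader ones on the bounded scale, and up to about 12 with other within-band shapes. Power for 3 points falls from 80% at SD 5 to 65% at 6, 52% at 7 and 29% at 10. All SDs other than 5 rest on assumed band shares, so these figures show how sensitive the claim is; they do not estimate the trial's actual power.

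**What to change.** Enrolment stays at 100.

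1. **Sample Size Calculation.** Delete the word *conservatively* unless a source SD from a comparable cohort supports it. State that the 80% power is conditional on an SD of 5. Add power, detectable difference and expected 95% confidence interval half-width over a range of SDs labelled as assumed, as in the last table above.
2. **Interpretation.** State that a non-significant result whose 95% confidence interval still contains a 3-point benefit will be reported as inconclusive, not as evidence of no effect.
3. **Statistical Analysis.** Add a linear regression of the 3-month LARS score on treatment with the covariates already prespecified, or a short prognostic subset such as anastomotic level. Logistic regression, the only adjusted model named, does not model a continuous score. Covariates that predict the score would reduce the residual SD; by how much cannot be judged from the article.

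Cost: items 1 and 2 are wording, and the stated power becomes less favourable. Item 3 is a small analysis change, with one extra model to fit. The article reports that no participant had been enrolled at submission, so all three can be settled before data exist.
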